## Methods

After explaining the fundamentals of the study to the patients and accepting their participation, they will sign the informed consent form. The first procedure will be to perform a symptom-limited treadmill exercise test with oxygen consumption, seven to ten days after hospital discharge, using the Bruce protocol. If the test results allow inclusion in the study, demographic data, clinical history, physical examination and analytical data will be completed in the data collection notebook. The baseline surveys will be completed, the procedures to be followed will be explained, as well as the schedule of the various activities included in each of the groups. Patients shall receive medication as deemed appropriate by the physician at the time of discharge from hospital, with the initial goal of achieving LDL of 70 mg/dl or less, blood pressure of 140/90 mmHg or less and, where appropriate, glycosylated haemoglobin of less than 7%.

The follow-up period will be 10 months in both groups. The differences in follow-up are detailed below.

At the end of the 10-month follow-up period, all subjects included in the study will undergo a stress test, final analysis and completion of the various outcome evaluation surveys.

Control Group A.

Patients in Control Group A will come to the hospital twice a week during the 8 weeks of the conventional rehabilitation program. Eight sessions will be devoted to physical exercise and another eight sessions to education in various aspects. At the end of the hospital phase, outpatient follow-up by primary and specialised care will be carried out. Subjects will visit the hospital a total of 16 times during 8 weeks to perform the exercises included in the hospital protocol, supervised by a physiotherapist and a nurse from the Cardiology Service.

The protocol includes:

Preparation to start the activity (Warm-up).

15 minutes of low impact cardiovascular exercise plus stretching and flexibility.

Stretching:

8-10 seconds interspersed with activities that maintain heart rate such as walking in place.

Musculature involved: triceps sural, hamstrings, quadriceps, deltoids, paravertebral and pectoralis.

The circuit:

The circuit is designed to cater for all patients with varying functional abilities. It provides the opportunity to increase cardiovascular work time. It is organised as explained in the following diagram:

| **LEVEL** | Group session content |
| --- | --- |
| 1 | 1 CV station followed by 1 min. Of AR |
| 2 | 2 CV stations followed by 1 min. Of AR |
| 3 | 3 CV stations followed by 1 min. Of AR |
| 4 | 4 CV stations followed by 1 min. Of AR |
| 5 | 5 CV stations followed by 1 min. Of AR |

- Warm-up
- Together with physiotherapist
- CV work (circuit)
- Individual work (levels)

**Part 1**

**15 min**

**Part 2**

**30 min**

- Cooldown + Stretching
- With Physiotherapist

**Part 3**

**15 min**

[figure not shown]

Educational program consisting in 8 talks about the following topics:

Supervised physical exercise program

[figure not shown]

[figure not shown]

[figure not shown]

**ACTIVE RECOVERY AREA (AR)**

***CV Station 2***

LIFT

KNEES

***CV Station 3***

FOOT

BACK

***CV Station 5***

UP/DOWN

STEP

***CV Station 5***

FOOT SIDEWAY

***CV Station 3***

WALK

DISTANCE

Supervised physical exercise programme

[figure not shown]

[figure not shown]

[figure not shown]

**ACTIVE RECOVERY AREA (AR)**

***CV Station 2***

LIFT

KNEES

***CV Station 3***

FOOT

BACK

***CV Station 5***

UP/DOWN

STEP

***CV Station 5***

FOOT SIDEWAY

***CV Station 3***

WALK

DISTANCE

- Hypertension and cholesterol

- Coronary heart disease

- Cardiovascular drugs

- Heart disease and sex

- Diabetes

- Physical exercise

- Diet

- Tabaco

Intervention Group B.

The patients in Intervention Group B, included in the telerehabilitation program, will attend the hospital twice a week for 2 consecutive weeks, carrying out three sessions of physical exercise and four sessions of education on the same subjects as control group A. Subsequently, they will follow the guidelines programed in the ITS by carrying out their guided physical activities and adherence to the guidelines for management of their risk factors until the end of the study period. All the data generated are recorded in the professional application.

The program consists of two phases: an outpatient phase, in which the patient will attend the hospital 4 times during two weeks; and a second long-term phase of 10 months, where the patient will carry out the entire rehabilitation and prevention program with total independence.

Hospital phase: Starting on the first day, each individual in the patient team is provided with the ITS system described in the materials section. The patient is instructed to perform the programed physical activity and how to use the instrumentation, consisting of the application on the smartphone and the web connection to access the educational content and control of recommended hygienic and dietary measures, as well as monitoring of the pharmacological treatment. Ambulatory physical activity consists of walking at a sustained pace, until the effective heart rate equal to 75% of the maximum heart rate, obtained in the baseline stress test, is reached. The intensity of the exercise will be individually adapted according to the result of this same test. The hospital stay will be about two and a half hours, according to the following schedule:

1st session (Monday)

- Data collection: 60m

- Lecture: Explanation of the program and how the system works: 30m

- First exercise session: 60m

2nd session (Thursday)

- Clarification of doubts about how the system works: 30m

- Talk: Coronary heart disease and cardiovascular risk factors: 40m

- Second exercise session: 60m

3rd session (alternate weeks, Mondays) (12 patients)

- Talk: Anxiety and depression. Strategies to resolve conflicts: 45m.

- Talk: Sexuality and smoking: 45m

- Sketches humour: 30m

4th session (Thursdays)

- Talk: Hypertension and diabetes: 30m

- Talk: Diet and nutrition: 30m

- Third exercise session: 60m

Ambulatory phase: from week 3 until the end of the trial at week 40, the patient should perform his physical exercise routines 4 times per week monitored by the ITS. These routines can be performed by walking outdoors. The patient's application on the mobile phone, allows the heart rate to be calculated for each exercise session. The system alerts about possible deviations from the programed training heart rate so that the patient can adjust their physical activity to achieve the recommended frequency. All this data is also transmitted to the platform for subsequent analysis by the professional. The application is not only a means of controlling and monitoring the quality of physical exercise, but also fundamentally a tool to assist in cardiovascular prevention in a comprehensive way. This means that the patient's cardiovascular risk factors will be recorded, in order to help the patient modify their lifestyle and correct or minimise the risk factors that contribute to disease progression. The support website includes personalised aids (information, education, motivational messages) so that the patient can self-manage their daily life and feel protected and in control.

The educational program will consist of 6 lectures on the following topics:

- Telerehabilitation program

- Information on coronary heart disease and cardiovascular risk factors.

- Anxiety and depression in the context of an acute coronary event.

- Sexuality and return to work after an acute coronary event

- Heart-healthy diet and the benefits of physical exercise.

- Smoking.

The technology available to patients in the telerehabilitation group includes the following:

A. Comprehensive telerehabilitation system

The Integral Telerehabilitation System (ITS) is a software and services platform created by Nabelia (http://nabelia.com/es/) to establish Cardiac Prevention and Rehabilitation Programs (CPRP) aimed at helping the management and personalised management of cardiovascular risk factors, with the highest quality but in a cost-effective manner for the healthcare centre and professionals. Its objective is to provide continuous, long-term care and support to patients with CVD during their recovery process.

The ITS to be configured for the study consists of the following elements:

1) Web-based application for the practitioner in the hospital, which allows to:

o Advise the patient on their personal care plan

o Create/modify standard plans to suit individual needs and personal goals

o Establish the patient's risk profile and targets for improvement

o Assess overall and CVRF status by means of aggregate indicators

o Long-term monitoring of the evolution of CVRFs and events that have occurred

o Advise the patient on long-term CVRF self-management strategies

For its part, the system is able to:

o Dynamically stratify patients according to risk, and supports the practitioner in assessing the need for unscheduled interventions, generating alerts when the parameters entered are outside the pre-set range.

o Provides decision support for the hospital or risk management service provider.

o Provides a workflow of procedures and follow-up interventions, and guides and reminds the patient of each step to improve adherence.

o Automatically generates advice and motivational messages to the patient based on the risk factors and circumstances present at any given time.

2) Patient applications

*Mobile phone software with the following functions:*

o Tasks

- Scheduled exercise sessions

- Medication reminders

- Reminder to take measurements (weight, blood pressure, heart rate, etc.)

o My status: personal information of:

- Care plan: medication, measurements, and physical activity

- Status of the risk factors present, objectives, evolution, and advice

- Results of the last data added (measurements, questionnaires, tasks carried out).

o Messages: Inbox of messages from the system and messages generated by professionals in a personalised way for a specific patient.

o Training monitor: guides the patient in carrying out their exercise.

*Patient website with the following services:*

o Profile and personal data.

o Evolution of aggregate indicators. History of the measurements introduced, and tasks carried out. Achievements.

o Access to health information aimed at certified patients: Salupedia, news, blogs, youtube, etc.

o Health literacy programs.

o Motivational programs.

3) Patient sensor equipment

The cardiac monitor is a comfortable compression garment that is designed for easy donning and adaptable to various physical conformations of the patient's chest. The garment has two textile electrodes from which a monopolar ECG signal is recorded. The electronics built into the garment processes this signal and transmits the data - using Bluetooth connection - to the mobile phone application. The measured data are:

o Instantaneous and average heart rate.

o Calories. METs, distance, speed, GPS position

o Exercise quality index (% of target achievement).

## Data collection

The following data shall be collected on all patients at baseline, at 4 months and at 10 months.

1. Demographic data: initials of name, age, sex, identification number).

2. Clinical data: STEMI, NSTEMI, unstable angina, stable angina, number of vessels, number of stents, complete revascularisation, active smoking, ex-smoker, hypertension, dyslipidaemia, diabetes mellitus, left ventricular ejection fraction, beta-blockers, ACEI/ARBs, statins, dual antiplatelet therapy.

3. Socio-occupational data: active worker, return to work after discharge.

1. Physical examination: systolic blood pressure, diastolic blood pressure, heart rate, body mass index (BMI), waist circumference, hip circumference.
2. Analytical data: glucose, creatinine, total cholesterol, LDL cholesterol, HDL cholesterol, triglycerides, CRPus, HbA1c.
3. Pulse wave velocity.
4. Surveys: EQ-5D, IPAQ, HAD, Adherence to Mediterranean diet, Fagerström test (if active smoking).
5. Clinical events: emergency department, readmission, revascularisation.

The following data will only be collected at baseline and at 10 months.

1. Exercise test: VO2max, exercise time, maximum heart rate, maximum blood pressure, recovery time, ST decline, angor.

The following data will only be collected from patients in the intervention group:

1. Every 15 days: weight, smoking, waist circumference, systolic pressure, diastolic pressure, heart rate, visual anxiety-depression thermometer, fruit consumption, vegetables, wine/beer consumption.

2. At 4 and 10 months: survey of satisfaction with the application.

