## Secondary Objectives

Very the improvement of the following parameters, after the intervention:

- Demonstrate an increase in oxygen consumption (VO2max).

- Demonstrate increased exertion time.

- Demonstrate an increase in workload.

- Decrease the presence of symptoms.

- Obtain improvement in lipid profile

- Decrease in ultrasensitive C Reactive Protein (CRPus)EQ

- Demonstrate increased adherence to the Mediterranean diet.

- Demonstrate improved results in psychological state.

- Demonstrate increased willingness to quit smoking and smoking cessation.

- Demonstrate a decrease in the sedentary lifestyle indicator.

- Improved measurement of carotid-femoral pulse wave velocity.

- To evaluate the cost per patient/month in the control cases of conventional rehabilitation and extended tele-rehabilitation intervention.

- To evaluate the time to return to work.

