**CLINICAL DATA**

| Unstable angina (Y/N) |  |
| --- | --- |
| NSTEACS (Y/N) |  |
| STEACS (Y/N) |  |
| Number of vessels (n) |  |
| Number of Stents (n) |  |
| Bypass Number (n) |  |
| Complete revascularisation (Y/N) |  |
| Diabetes mellitus (Y/N) |  |
| Arterial hypertension (Y/N) |  |
| Dyslipidaemia (Y/N) |  |
| Active smoking (Y/N) |  |
| Ex-smoker (Y/N) |  |
| Ejection fraction (%) |  |

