**ADITIONAL MEDICATION**

| Beta-blockers (Y/N) |  |
| --- | --- |
| Calcium antagonists (Y/N) |  |
| Nitrates (Y/N) |  |
| Anti-aggregants (Y/N) |  |
| ACE inhibitors / ARBs (Y/N) |  |
| Lipid lowering agents (Y/N) |  |
| Others (Y/N) |  |

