**VISIT 2 // MONTH 4**

**FILIATION DATA**

| Patient initials |  |
| --- | --- |
| Patient identification code (n) |  |
| Randomisation number (n) |  |
| Date (DD-MM-YY) |  |

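### The data-collection text, schedule table, analysis section and CRF contradict each other on month-4 surveys and pulse wave velocity and on follow-up smoking and medication data

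*Protocol*

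**What the plan says.** Section 6.5, Data collection, opens its main list with "The following data shall be collected on all patients at baseline, at 4 months and at 10 months". That list includes "Surveys: EQ-5D, IPAQ, HAD, Adherence to Mediterranean diet, Fagerström test (if active smoking", and pulse wave velocity. Under clinical data it includes "complete revascularisation, active smoking, ex-smoker, hypertension, dyslipidaemia, diabetes mellitus" and "beta-blockers, ACEI/ARBs, statins, dual antiplatelet therapy". A separate short list confines the exercise test to baseline and month 10. A third list, for the intervention group only, includes smoking among items recorded every 15 days.

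Section 6.6, Outline of proceedings, marks surveys and pulse wave velocity at the start and month 10, and clinical data and physical examination at the start only.

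In Annex 1, the pages under "VISIT 2 // MONTH 4" cover identification, physical examination, blood tests, clinical events and work status. The month-10 visit adds the stress test, arterial stiffness and the surveys. The lines "Active smoking (Y/N" and "Lipid lowering agents (Y/N" appear at Visit 1 only.

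Section 9.3 plans between-group comparisons of the primary and secondary variables at baseline, 4 and 10 months, and within-group tests at 4 or 10 months. Section 7.3 takes the primary variable from IPAQ and lists smoking and statins among the secondary variables. The secondary objectives include "Demonstrate increased willingness to quit smoking and smoking cessation".

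**The concern.** Section 5 makes the data collection logbook the place where all necessary data are recorded, and Annex 1 is that logbook. Sites will complete the fields it contains. Monitoring (section 11) checks that logbook entries agree with the clinical history, which would not readily expose a field that was never printed. A contradiction between the text and the CRF is therefore likely to be settled in favour of the CRF without anyone deciding so.

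Two things are at stake. First, the 4-month comparisons of survey scores and pulse wave velocity would be planned but have no data, and a questionnaire about the last 7 days cannot be completed months later. Second, cessation would be ascertained differently in the two arms of an unblinded trial. In controls the only smoking item on the CRF after baseline is the month-10 Fagerström score. Because it is due only in active smokers, a blank cannot separate a patient who has quit from a form that was not completed.

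The medication gap is a lesser matter but of the same kind. Lipid improvement is an objective, lipids are measured at months 4 and 10, and a need to change lipid-lowering treatment is a withdrawal criterion (section 6.3). Yet no follow-up CRF field records that treatment.

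**Working it through.** No figure in the protocol is in dispute, so the check is an item-by-item comparison. Entries are the months at which each source calls for the item.

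| Item | Text, 6.5 | Table, 6.6 | CRF, Annex 1 |
| --- | --- | --- | --- |
| Surveys, including IPAQ | 0, 4, 10 | 0, 10 | 0, 10 |
| Pulse wave velocity | 0, 4, 10 | 0, 10 | 0, 10 |
| Smoking status | 0, 4, 10 | 0 (clinical data row) | 0 |
| Statins / medication | 0, 4, 10 | 0 (clinical data row) | 0 (lipid-lowering agents, yes/no) |
| Physical examination | 0, 4, 10 | 0 | 0, 4, 10 |
| Blood tests | 0, 4, 10 | 0, 4, 10 | 0, 4, 10 |
| Exercise test | 0, 10 | 0, 10 | 0, 10 |

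1. **Month-4 surveys and pulse wave velocity.** Table and CRF agree with each other and contradict the text. IPAQ is the only stated source of METs-minutes/week, so a 4-month comparison of the primary variable has no input under the CRF. The same holds for pulse wave velocity, a secondary variable in 7.3, and for HAD, diet and EQ-5D. Those scores are not itemised in 7.3, but 6.5 schedules them at month 4. Diet and psychological state are secondary objectives, and quality of life enters the economic evaluation in 9.4.

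2. **Smoking status.** The text asks for it at three visits; table and CRF have it at one. After baseline, controls have the month-10 Fagerström score, conditional on smoking. The telerehabilitation arm has that score and the 15-day entries. No post-baseline status field is common to both arms.

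3. **Medication.** The text asks for statins at three visits; the CRF has a single yes/no line for lipid-lowering agents at Visit 1. Section 13.5 says both that follow-up physicians may modify discharge drugs and that doses will not change except for high LDL at 4 months. Those statements must be reconciled. On either, the follow-up CRF cannot show whether treatment changed.

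4. **Physical examination.** Here text and CRF agree and the table is the odd one out. The data are collected; only the table needs correcting.

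5. **Month-10 IPAQ.** Text, table and CRF all include it, and the general objective is set at 10 months.

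Extent under the table and CRF: no month-4 value of IPAQ, HAD, diet, EQ-5D or pulse wave velocity for any of the 60 planned patients, and a smoking-status or medication field at 0 of 2 follow-up visits.

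**The case against.** The best defence is that section 9.3 is generic. It names all primary and secondary variables at all three visits, yet the exercise test, a secondary variable, is deliberately not done at month 4. So 9.3 may mean at the visits where each variable is measured. The opening of 6.5 is also loose: read literally, it asks for sex, infarct type and number of vessels at every visit. Medical history is a named data source, which might supply smoking and drug information. And 6.5 does require collection, so data are lost only if the table and CRF prevail.

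The point about 9.3 is fair as far as it goes. It does not rescue the surveys or pulse wave velocity, because 6.5 puts them in the three-visit list and names the exercise test separately as the exception. Nor is smoking status a fixed trait like sex; its change is an objective. Retrieval from medical notes is possible, but nothing says it will be done for smoking, or done alike in both arms. The conditional nature of the data loss stands, and it is why this is a contradiction to resolve rather than a demonstrated loss.

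A reader might go further and infer that about 7 patients (0.12 × 60 = 7.2, the expected loss) will have no post-baseline IPAQ at all. The protocol does not support that. Section 12.2 calls for patients who leave to have the end-of-study evaluation, which includes IPAQ, so only those who do not return would lack it. The timing of losses is not stated.

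**Conclusion.** The contradiction is real and should be resolved. If the table and CRF are followed, the planned 4-month comparisons of IPAQ, HAD, diet, EQ-5D and pulse wave velocity have no data in either arm. Cessation then rests on indirect evidence in controls and on richer evidence in the telerehabilitation arm. Lipid-lowering treatment after baseline is not recorded on the CRF, although 6.5 asks for statins at each visit.

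Three limits apply:

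- The 10-month primary endpoint is not touched. A reader might take missing month-4 IPAQ as a threat to the primary analysis, but only the additional 4-month look at that variable is affected.
- Cessation is poorly and asymmetrically captured. It would be too strong to say that all later smoking data are absent or that cessation cannot be analysed: the Fagerström score is on the month-10 CRF for both arms, and 15-day entries exist in one. Nothing in the protocol proposes to judge cessation from those entries.
- Follow-up physical examination is not lost, since the CRF has it at both visits. Section 9.3 plans no analysis that names statins specifically, so that gap concerns a listed secondary variable and the reading of lipid results, not a named model.

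The conclusion assumes that sites work from Annex 1 as printed.

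**What to change.** - **Surveys.** Add the existing survey page to the month-4 CRF visit and mark month 4 in the survey row of 6.6. Alternatively, remove surveys from the month-4 list in 6.5 and delete the 4-month survey comparisons from 9.3 and its summary in 1.15. Either resolves the conflict; a different analysis model is not needed.
- **Smoking.** Add the active-smoking yes/no line to the month-4 and month-10 CRF visits in both arms, and state that cessation is judged from those common visits.
- **Medication.** Add the medication lines to both follow-up visits, with lipid-lowering treatment and any change in it. Repeating the yes/no line alone would not show a change of drug or dose.
- **Schedule.** Decide whether pulse wave velocity is measured at month 4 and make 6.5, 6.6, 9.3 and Annex 1 agree. Mark physical examination at months 4 and 10 in 6.6, or remove it from 6.5 and the CRF. Bring the clinical data row into line with the smoking and medication lines.

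The cost is a CRF revision, the matching protocol edits, and questionnaire time at a month-4 visit that already takes place. Measuring pulse wave velocity at month 4 would add an ultrasound examination; dropping it from that visit costs nothing.

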## Outline of proceedings

|  | **Start** | **4 months** | **10 months** |
| --- | --- | --- | --- |
| **INFORMED CONSENT** | X |  |  |
| **FILIATION DATA** | X | X | **X** |
| **CLINICAL DATA** | X |  |  |
| **SOCIO-OCCUPATIONAL DATA** | X | X | X |
| **PHYSICAL EXPLORATION** | X |  |  |
| **PWV** | X |  | X |
| **BLOOD TEST** | X | X | X |
| **STRESS TEST** | X |  | X |
| **PHYSICAL WORKING CAPACITY** | X |  | X |
| **SURVEY** | X |  | X |
| **CLINICAL EVENTS** | X | X | X |
| **COST-EFFECTIVENESS ANALYSIS** |  |  | X |

